### **Safety endpoints specifically for PEPaNIC**

The clinical research team guarantees a daily follow-up of patient screening and inclusion, availability of requested clinical data in the clinical patient files and protocol compliance. Each non-compliance to the protocol and other questions or problems are reported to the study monitor and discussed with the principal investigators. Serious Adverse Events (SAE) are also reported to the study coordinating investigator/project leader (K.U.Leuven). The study monitor regularly provides the sponsor with reports on inclusions and SAE. Regular meetings are organized with principal investigators and clinical research team to discuss the daily progression of the research project.

As patients not receiving early PN may be considered at increased risk for hypoglycemia, we will report for both groups the number of patients experiencing hypoglycemia <40 mg/dl during the time window of the randomized intervention.

Hypoglycemia resistant to parenteral glucose administration, or with clinical symptoms, is considered as a SAE and the incidence during the time window of the randomized intervention will be reported for both groups. In addition, overall blood glucose control during the time window of the intervention will be compared using daily morning blood glucose as well as daily maximal and minimal blood glucose.

Further safety endpoints comprise vital status, hypoglycemia, SAEs and complications related to the mode of nutrition. Survival up to 90 days after randomization in both treatment groups will be compared by Kaplan Meier survival plots. The impact of "late PN" versus "early PN" will be analyzed, with and without correction for risk factors, by Cox proportional hazard analysis. In addition, we will record in-ICU and in-hospital mortality, and will analyze differences with Chi-square testing. As the randomized study intervention only takes place during a time window up to the 8th day in ICU, we also plan to analyze early lethality within this time window in the intention-to-treat population as part of the safety analysis.

Safety issues also comprise the occurrence of feeding-mode-related complications during the time window of the intervention. Therefore, occurrence of these complications (digestive intolerance, complicated insertion of feeding tubes, pneumothorax, haemothorax and subclavian or carotid artery puncture, occlusion or displacement of central venous catheters or gastric feeding tubes) will be reported for both treatment groups.

Above mentioned SAE's and safety endpoints will be handled and reported within the standard timeframe as described above.

#### **8.2.1 Suspected unexpected serious adverse reactions (SUSAR)**

Not applicable

#### **8.2.2 Annual safety report**

Not applicable

#### **8.3 Follow-up of adverse events**

All adverse events will be followed until they have abated, or until a stable situation has been reached. Depending on the event, follow up may require additional tests or medical procedures as indicated, and/or referral to the general physician or a medical specialist.

#### **8.4 Data Safety Monitoring Board (DSMB)**

The coordinating investigator/project leader (K.U.Leuven) provides direct access to the CRF, the source data and the study master file for monitoring, Independent Ethics committee review and regulatory inspection. The coordinating investigator/project leader (K.U.Leuven) established an independent data safety monitoring board (DSMB) (Prof. dr. [name], Prof. dr. em. [name], Prof. dr. em. [name], Prof.dr. [name] (statisticus)), which holds no conflicts of interest with the sponsor or coordinating investigator/project leader (K.U.Leuven). The coordinating investigator/project leader (K.U.Leuven) appoints one monitor. The monitor verifies that the trial is performed in accordance to the protocol as described in the European Medicine Agency's "Note for guidance on good clinical practice CPMP/ICH/135/95" as well as the Declaration of Helsinki. Monitoring will be performed and will be reported following the sponsor's standing operating procedures. No fault insurance is covered by Fortis Corporate Insurance NV (Leuven) and Akkermans Van Elten Assurantiën BV (Rotterdam).

One formal "safety" interim analysis will be planned after patient number 720 has left the ICU, during which the independent DSMB will have access to un-blinded results on ICU mortality, hospital mortality and serious adverse events. The DSMB will

then judge on whether or not to prematurely stop the clinical trial for safety reasons, or to perform more safety interim analyses. The DSMB will advise on eventual continuation of the study to completion, under monitoring of the serious adverse event. Because the primary efficacy

endpoint will not be analyzed, no correction of the significance level at the final analysis will be necessary.

The advice(s) of the DSMB will be notified upon receipt by the sponsor to the METC that approved the protocol. With this notification a statement will be included indicating whether the advice will be followed.

## 9. STATISTICAL ANALYSIS

### 9.1 Descriptive statistics

The current statistical analysis plan comprises the primary and secondary clinical endpoints of this RCT (work package 1). These include the acute clinical effects of the intervention during ICU stay and hospitalization, including survival up to 90 days after randomization.

The sample size (N=1440, 720 per arm) is calculated in order to detect, with at least 80% power (one- tailed; the two-tailed power is 70%) and 95% certainty, a reduction in PICU infections from 20% to 15% and, with at least 90% power (2-tailed) and 95% certainty, a reduction in mean duration of stay in PICU of 1 day. With this sample size, and for safety reasons, also any substantial impact on mortality (increase or decrease with an absolute +/- 2%, although unexpected taken the adult data), can be excluded with a power of around 62-75% depending on the true mortality in the total population. We plan to calculate the true power of the study for detection of any eventual smaller differences in these outcomes.

#### ***General rules of the statistical analysis***

All analyses will be done on intention to treat basis. The analyses will be performed on the whole set of patients and by subgroups of patients based on the primary diagnostic categories used as prognostic factors for stratification and on septic/non-septic groups of patients.

A consort diagram will be reported. The data file will be finalised 90 days after inclusion of the last patient. To assess compliance with the study protocol, the amounts of PN and EN actually given in the two study groups during the intervention window of 7 days will be reported as absolute numbers and percentages of target calories. Discrete variables will be summarised by frequencies and percentages and analysed by (exact) Chi- square test or logistic regression analysis. Continuous variables will be summarised by use of either mean or standard deviations (SD) or median and interquartile range as appropriate and compared using Student's t-test or Mann-Whitney-U test, as appropriate. Time to event analysis will be performed by Cox proportional hazard analysis. All outcomes will be analysed in an uncorrected manner as well as (jointly) corrected for risk factors (type and severity of illness, age, on admission nutritional status and risk scores). *A priori* defined subgroup analyses will be performed for patients admitted to ICU after cardiac surgery as compared with all other patients; for patients with and without sepsis upon admission; for patients with contra-indications for EN on admission or not. For all endpoints, differences will be considered statistically significant whenever the p-value is lower than 0.05 without correction for multiple testing.

#### Safety endpoints

Safety endpoints comprise vital status, hypoglycaemia, serious adverse events and complications related to the mode of nutrition. Survival up to 90 days after randomization in both treatment groups will be compared by Kaplan Meier survival plots. The impact of "late PN" versus "early PN" will be analyzed, with and without correction for risk factors, by Cox

proportional hazard analysis. In addition, we will record vital status at ICU and hospital discharge, and will analyze differences with Chi-square testing. As the randomized study intervention only takes place during a time window up to the 8th day in ICU, we also plan to analyze early lethality within this time window in the intention to treat population as part of the safety analysis.

## **9.2 Univariate analysis**

Discrete variables will be summarized by frequencies and percentages and analyzed by (exact) Chi-square test or logistic regression analysis. Continuous variables will be summarized by use of either mean or standard deviations (SD) or median and interquartile range as appropriate and compared using Student's t-test or (exact) Mann-Whitney-U test, as appropriate. Time to event analysis will be performed by Cox proportional hazard analysis. Time to discharge alive from ICU will be reported by Kaplan-Meier plots, with ICU non-survivors censored beyond the longest ICU stay of survivors and censoring time of patients still in the ICU at closing of the data file (90 days after last patient inclusion) over both treatment groups. The impact of "late PN" versus "early PN" will be analyzed, with and without correction for age, nutritional status and risk categories and type and severity of illness, by Cox proportional hazard analysis. The distribution of the actual time to discharge from ICU will be reported for ICU-survivors and ICU-non-survivors separately. In view of the time window of the randomized intervention in ICU, also the proportion of patients staying beyond 8 days in ICU will be reported.

## **9.3 Multivariate analysis**

All outcomes will be analyzed in an uncorrected manner as well as (jointly) corrected for risk factors (type and severity of illness, age, on admission nutritional status and risk scores). Another *a priori* defined subgroup analysis will be performed for patients admitted to ICU after cardiac surgery as compared with all other patients. Also an *a priori* subgroup analysis is planned for patients with and without sepsis upon admission.

All analyses will be performed uncorrected as well as corrected for age, nutritional status and risk categories and type and severity of illness. Time-to-event analysis will be analyzed similarly as the primary endpoint. Proportion of patients requiring support of vital organ functions and distribution of duration of support will be analyzed by non-parametric or parametric testing depending on the normality of the distribution in the subgroup of patients for which support was needed. Proportions will be compared using chi-square testing. Results of repeated measurements will be analyzed using an appropriate model for longitudinal data.

a. Time to final (alive) weaning from mechanical respiratory support: patients still on mechanical respiratory support at closing of the data file (90 days after last patient inclusion) will be censored at that time point. ICU non-survivors will be censored beyond the longest duration of mechanical respiratory support of the survivors.

b. Kidney failure: Proportion of patients in need for renal replacement therapy (RRT) during ICU stay; distribution of duration of RRT (for those patients requiring RRT); proportion of patients with a post-randomization diagnosis of new kidney injury/failure (defined by modified Risk, Injury, Failure, Loss, and End-stage Kidney (RIFLE) classification criteria as a plasma creatinine doubling or more during ICU stay) in both treatment groups. In addition, the duration of a score RIFLE $\geq$ 2 will be used as a marker of time to recovery of kidney damage.

c. Need for pharmacological or mechanical hemodynamic support during ICU stay, and duration of such need.

In addition, time to final (alive) weaning from all pharmacological or mechanical hemodynamic support in ICU will be analyzed, with ICU non-survivors censored beyond the longest duration of pharmacological or mechanical hemodynamic support of the survivors and censoring time of patients still on such support at closing of the data file (90 days after last patient inclusion) over both treatment groups.

d. Number of readmissions to the PICU.

e. Liver dysfunction: Proportion of patients during the time window of the intervention and during the whole ICU stay presenting with cholestatic or cytolytic liver dysfunction will be compared.

f. Inflammation: Effect of the intervention on inflammation will be analyzed by comparing the distribution of the highest value reached during ICU stay and changes from baseline to the highest value and by comparing time profiles of daily C-Reactive Protein values.

g. Child health questionnaire scores (WEEFIM, HUI, CHQ) at hospital discharge in both treatment groups will be compared.

#### **9.4 Interim analysis**

As the previous study in adults has shown that lethality was not different among the study groups and that morbidity was prevented by withholding feeding, and since the participating centers are currently providing early PN, repeated interim analyses for efficacy are not required. However, one formal “safety” interim analysis will be planned after patient number 720 has left the ICU, during which the independent DSMB will have access to un-blinded results on ICU mortality, hospital mortality and serious adverse events. The DSMB will then judge on whether or not to prematurely stop the clinical trial for safety reasons, or to perform more safety interim analyses. The DSMB will advise on eventual continuation of the study to completion, under monitoring of the serious adverse event. Because the primary efficacy

endpoint will not be analyzed, no correction of the significance level at the final analysis will be necessary.

The safety analyses will be done on the whole set of patients and by subgroups of patients based on the primary diagnostic categories used as prognostic factors for stratification and on septic/non-septic groups of patients.

## **10. ETHICAL CONSIDERATIONS**

### **10.1 Regulation statement**

The study will be conducted in accordance to the protocol as described in the European Medicine Agency's "Note for guidance on good clinical practice CPMP/ICH/135/95" as well as the Declaration of Helsinki (*59th WMA General Assembly, Seoul, Korea, October 2008*) and in accordance with the Medical Research Involving Human Subjects Act (WMO).

### **10.2 Recruitment and consent**

The study protocol and consent forms will be sent for approval by the Institutional Review Board of the Katholieke Universiteit Leuven and the Erasmus MC (Lokale uitvoerbaarheid) and by the competent Belgian and Dutch authorities (CCMO). Written informed consent is obtained from the parents or the legal guardian by the investigator's team or one of the supervising doctors, who will inform the parents of the patients (and the patients themselves if the age is > 12 years) and ask for their consent. The parents / legal guardians and (if applicable) the patients will receive a patient information letter and an informed consent form.

Written informed consent will be obtained from the patient or the closest family member or legal guardian. For planned PICU admissions after elective procedures, informed consent will be asked beforehand, if possible.

For emergency PICU admissions, treatment allocation will be done after assessment of the patient for eligibility by the attending physician within the time frame of two hours. If eligible, the patient will be randomized into the study and the allocated glucose infusion (with micronutrients) will be started. Informed consent will be asked within the time frame of 24 hours (deferred informed consent) as a nutritional regimen has to be initiated already on admission. When consent is given, the allocated nutritional regimen will proceed (Early (with additional lipids and protein targeting nutritional goals < day3) vs Late (no PN)). When NO consent is given, the nutritional regimen and glucose infusion will be placed under responsibility of the supervising clinical team of doctors.

The parents or legal guardians can withdraw the patient from the study at any time, without penalty or impact on treatment.

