### **15.4 Sample size calculation**

The sample size (N=1440, 720 per arm) is calculated in order to detect, with at least 80% power (one-tailed; the two-tailed power is 70%) and 95% certainty, a reduction in PICU infections from 20% to 15% and, with at least 90% power (two-tailed) and 95% certainty, a reduction in mean duration of stay in PICU of 1 day. With this sample size, and for safety reasons, also any substantial impact on mortality (increase or decrease with an absolute +/- 2%, although unexpected taken the adult data), can be excluded with a power of around 62-75% depending on the true mortality in the total population. We plan to calculate the true power of the study for detection of any eventual smaller differences in these outcomes.

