### ***Blinding of treatment allocation***

Treating physicians and patients cannot be blinded. All outcome assessors, which are investigators not directly involved in the patients care (such as statisticians, laboratory personnel, infectious disease specialists, pathologists and physiotherapists involved in the strength measurement) as well as physicians and nurses in the conventional wards are blinded to treatment allocation.

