#### **18.5 Replacement of individual subjects after withdrawal**

Subjects that withdraw after randomization has been conducted will not be replaced, subjects that have not been allocated and withdraw after signing the consent form but before the start of randomization will be replaced.

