#### **18.6 Follow-up of subjects withdrawn from treatment**

A register is kept of all patients evaluated for inclusion and of patients who withdraw from the study. The latter are clinically followed up without their data being analyzed in the study, according to intention-to-treat analysis.

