### ***General rules of the statistical analysis***

All analyses will be done on intention to treat basis. The analyses will be performed on the whole set of patients and by subgroups of patients based on the primary diagnostic categories used as prognostic factors for stratification and on septic/non-septic groups of patients.

A consort diagram will be reported. The data file will be finalised 90 days after inclusion of the last patient. To assess compliance with the study protocol, the amounts of PN and EN actually given in the two study groups during the intervention window of 7 days will be reported as absolute numbers and percentages of target calories. Discrete variables will be summarised by frequencies and percentages and analysed by (exact) Chi- square test or logistic regression analysis. Continuous variables will be summarised by use of either mean or standard deviations (SD) or median and interquartile range as appropriate and compared using Student's t-test or Mann-Whitney-U test, as appropriate. Time to event analysis will be performed by Cox proportional hazard analysis. All outcomes will be analysed in an uncorrected manner as well as (jointly) corrected for risk factors (type and severity of illness, age, on admission nutritional status and risk scores). *A priori* defined subgroup analyses will be performed for patients admitted to ICU after cardiac surgery as compared with all other patients; for patients with and without sepsis upon admission; for patients with contra-indications for EN on admission or not. For all endpoints, differences will be considered statistically significant whenever the p-value is lower than 0.05 without correction for multiple testing.

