### **21.2 Recruitment and consent**

The study protocol and consent forms will be sent for approval by the Institutional Review Board of the Katholieke Universiteit Leuven and the Erasmus MC (Lokale uitvoerbaarheid) and by the competent Belgian and Dutch authorities (CCMO). Written informed consent is obtained from the parents or the legal guardian by the investigator's team or one of the supervising doctors, who will inform the parents of the patients (and the patients themselves if the age is > 12 years) and ask for their consent. The parents / legal guardians and (if applicable) the patients will receive a patient information letter and an informed consent form.

Written informed consent will be obtained from the patient or the closest family member or legal guardian. For planned PICU admissions after elective procedures, informed consent will be asked beforehand, if possible.

For emergency PICU admissions, treatment allocation will be done after assessment of the patient for eligibility by the attending physician within the time frame of two hours. If eligible, the patient will be randomized into the study and the allocated glucose infusion (with micronutrients) will be started. Informed consent will be asked within the time frame of 24 hours (deferred informed consent) as a nutritional regimen has to be initiated already on admission. When consent is given, the allocated nutritional regimen will proceed (Early (with additional lipids and protein targeting nutritional goals < day3) vs Late (no PN)). When NO consent is given, the nutritional regimen and glucose infusion will be placed under responsibility of the supervising clinical team of doctors.

The parents or legal guardians can withdraw the patient from the study at any time, without penalty or impact on treatment.

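### Emergency admissions are randomised before consent in an open-label trial, and withdrawn patients' data go unanalysed: if refusals are treated as withdrawals, the analysed groups need not be the randomised groups

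*Supplement*

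**What the plan says.** Final protocol 21.2 (same wording as 10.2 of the original) sets the order for emergency admissions. Eligibility is judged within two hours. Then: "If eligible, the patient will be randomized into the study and the allocated glucose infusion (with micronutrients) will be started". Consent comes afterwards: "Informed consent will be asked within the time frame of 24 hours (deferred informed consent)". The stated reason is that some regimen has to begin on admission. If the parents agree, the allocated early or late regimen continues. If not: "When NO consent is given, the nutritional regimen and glucose infusion will be placed under responsibility of the supervising clinical team of doctors". That sentence covers feeding and says nothing about the child's data. Planned admissions are asked beforehand where possible.

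Section 18.2 states: "Treating physicians and patients cannot be blinded". The people asking for consent (the investigator's team or a supervising doctor) are not among the blinded roles listed there.

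Three further passages decide what happens to a child who leaves:
- 18.5: "Subjects that withdraw after randomization has been conducted will not be replaced".
- 18.6, on patients who withdraw: "The latter are clinically followed up without their data being analyzed in the study, according to intention-to-treat analysis".
- 20.1: "All analyses will be done on intention to treat basis".

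Section 20.1 also promises a CONSORT diagram, and 18.6 a register of patients evaluated and withdrawn. Neither says that refusals will be shown by arm.

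**The concern.** Central randomisation with an undisclosed block size conceals the allocation up to the moment of randomisation. In the emergency pathway the decision to take part comes after that moment, with the allocated infusion already running and the staff unblinded. Early PN is the centres' standard care. Late PN withholds it for a week, and the protocol itself names hypoglycaemia and underfeeding as its risks. Willingness to continue could therefore differ by arm, among parents or in how staff put the question.

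This matters only if refusers leave the analysis. The sentence in 18.6 points that way for withdrawals, and nothing says that refusers are treated otherwise. Dropping randomised children on a decision that can depend on the arm is what intention to treat is meant to prevent, and baseline adjustment cannot be relied on to undo it. The primary endpoints, new infections and time to live ICU discharge, would both be exposed.

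**Working it through.** **1. The plan's own figure.** Section 15.4: "The sample size (N=1440, 720 per arm) is calculated" for infections of 20% v 15%, with 80% one-tailed and 70% two-tailed power at the 5% level. Using the normal approximation with pooled variance under the null:
- null SE = √(2 × 0.175 × 0.825 / 720) = 0.02003
- alternative SE = √((0.16 + 0.1275) / 720) = 0.01998
- two-tailed: Φ((0.05 − 1.96 × 0.02003) / 0.01998) = 70.5%
- one-tailed, with 1.645: 80.3%

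Both stated figures reproduce.

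**2. The passages together.** 21.2 allows a refusal after randomisation and is silent on the data. 18.6 removes withdrawn patients' data. 18.5 does not replace them. 20.1 requires intention to treat. 18.6 and 20.1 agree only if intention to treat is taken to allow exclusion of randomised patients. Whether a refuser counts as withdrawn is not stated.

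**3. Size if refusers are dropped.** All of the following are assumptions, because the documents give none of these rates:
- emergency share f = 0.4 or 0.6
- refusal among emergencies r (early / late) = 5% / 10%, 5% / 15% or 10% / 20%
- refusers' infection risk q = 10%, 20% or 40%
- no treatment effect: 20% infected in each arm as randomised

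With x = f × r, the rate seen in an arm is (0.20 − x·q) / (1 − x), and 720 × (1 − x) children remain.

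Largest case (f = 0.6, 10% / 20%, q = 40%):
- early: x = 0.06, (0.20 − 0.024) / 0.94 = 18.72%
- late: x = 0.12, (0.20 − 0.048) / 0.88 = 17.27%
- late minus early = −1.45 points, and 1.45 / 5 = 29% of the target difference

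| f | Refusal early / late | Difference, q = 10% | q = 20% | q = 40% | Children left |
|---|---|---|---|---|---|
| 0.4 | 5% / 10% | +0.21 | 0 | −0.42 | 1397 |
| 0.4 | 5% / 15% | +0.43 | 0 | −0.87 | 1382 |
| 0.4 | 10% / 20% | +0.45 | 0 | −0.91 | 1354 |
| 0.6 | 5% / 10% | +0.33 | 0 | −0.66 | 1375 |
| 0.6 | 5% / 15% | +0.68 | 0 | −1.36 | 1354 |
| 0.6 | 10% / 20% | +0.73 | 0 | −1.45 | 1310 |

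Differences are late minus early in percentage points; a negative sign favours late PN. With equal refusal in the two arms the difference is 0 for every q.

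**4. Power under the same assumptions.** With 1397 to 1310 children left, two-tailed power for 20% v 15% is 69% to 66%, against 70.5% with 1440.

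**The case against.** **Disclosure of the arm is inferred.** No passage says parents learn the arm before deciding. Section 21.2 refers to an information letter and a consent form, which are not part of the text considered here and may use one wording for both arms. A reader might infer that parents decide knowing the allocation. The documents do not establish that; they show only that the order of events and the open-label design permit it. This stands.

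**Exclusion of refusers is also inferred.** 18.6 speaks of patients who withdraw, 21.2 is silent on data, and 20.1 promises intention to treat. If refusers are kept, the effect is dilution and the groups stay as randomised. This stands as a condition on the point. It does not remove it, because the only rule on the data of children who leave is the one in 18.6.

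**Arm-dependent refusal alone is not enough.** A reader might infer that it biases every endpoint. The middle column of the table shows otherwise: refusers must also differ in prognosis.

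**The SAP reports no shortfall.** It gives 1440 randomised, 717 late and 723 early. That gap of 6 is smaller than the 14 to 43 implied by the scenarios (705.6 − 691.2 and 698.4 − 655.2). The numbers left are therefore illustrations and should not be read as a forecast. Near-balance does not settle the matter either: the SAP does not say whether refusers are counted, and similar numbers do not show similar prognosis.

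**Masking the conversation is hard.** By 16.1 the infusions differ from day 1, so a consent-taker unaware of the arm at all hours is neither assured nor shown to be free of staffing cost. This stands and limits the fix.

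Deferral itself has a stated reason and is not criticised here.

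**Conclusion.** The point holds conditionally. Following the final protocol as written can remove randomised children from the analysis on a decision taken after allocation in an open-label trial, and 18.6 conflicts with 20.1 in calling that intention to treat. Bias requires three things together: refusers handled as withdrawals, refusal that depends on the arm, and refusers whose prognosis differs.

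Under the assumed rates the spurious infection difference is 0 to about 1.5 points in either direction, and the largest value comes from one corner of the range. The loss of two-tailed power is at most about 4 points. Both figures rest wholly on assumed refusal rates, refuser risk and emergency share. The point applies to emergency admissions and to any planned ones not asked beforehand.

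A reader might infer that refusal did differ by arm or that the trial's result is biased. The documents contain no evidence of either.

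**What to change.** - **21.2:** use one consent text for both arms. Where existing staff allow and the ethics committee accepts it, do not make the arm part of the consent conversation. Ask parents who refuse for permission to use infection, ICU-stay and vital-status data.
- **18.6 and 20.1:** replace the exclusion of withdrawn patients' data by analysis of every randomised child as allocated wherever permission exists. State that refusals of deferred consent fall under this rule.
- **20.1, CONSORT diagram:** report by arm the refusals, and the deaths or discharges that occurred before consent was sought.
- **15.4:** say whether 1440 counts randomised or consented children. This is a missing detail only.

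The cost is protocol and consent wording, slightly more consent and analysis work, and ethics committee agreement to the consent text and to the use of refusers' data. No feeding rule changes.
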